#### Gait function

As walking is by far the most important aspect of functional status, physical functioning will be objectively measured by means of gait analysis. The Timed Up and Go (TUG) test, the 4x10m self-paced walk test (SPWT), the stair-climb test (SCT) and the 30-s chair stand test (30s-CST) will be used to assess the physical performance. The TUG test measures the time needed for the patient to stand up from a chair, walk 3 m, turn, walk back to the chair and sit down. This test has been used to assess the functional activity [43]. For the SPWT the patient has to walk 10 m in a paced, but comfortable way and repeat this four times, for a total of distance 40 m [44]. The time the patient needs to cover this distance is measured, and the mean speed is calculated. For the SCT the patient is asked to ascend and then descend a stairs with 10 steps [45]. Finally, for the 30s-CST, the patient is asked to stand up and sit down in a chair as many time as possible. All four tests have been suggested as reliable and valid measures to compare outcomes after THA, and they are the recommended performance-based tests to assess the physical functioning before and after THA [45, 46].

#### Participation

To assess social participation, the subscale *Participation* of the World Health Organisation Disability Assessment Schedule II (WHODAS II) questionnaire [47, 48] will be assessed six weeks, three months and one year postoperatively. This subscale of the WHODAS II consists of 10 items asking about problems with participation in society. All questions are scored on a 5-item Likert scale ranging from no problem to extreme problems/cannot do. The last 30 days are taken into consideration when answering the questions. The Dutch version of the WHODAS II is considered valid and reliable [48].

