**Methods/design:**

A randomised controlled trial will be performed. Patients will be randomly allocated to undergo THA by means of the anterior or posterolateral approach. Both the intervention and control group will consist of two subgroups: 1) patients with a good bone stock who will receive an uncemented femoral stem, and 2) patients with a poor bone stock who will receive a cemented femoral stem. Patients between 18 and 90 years with primary or secondary osteoarthritis will be included. Physical functioning and health-related quality of life will be assessed by means of questionnaires. Additionally, performance based tests will be performed to objectively assess the physical functioning. Cost-effectiveness will be assessed by obtaining data on medical costs in and outside the hospital and other nonmedical costs. Measurements will take place preoperatively, two and six weeks, three months and one year postoperatively.

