### Measurements

Measurements will be performed by an independent investigator. Standard measurement will take place preoperatively, and six weeks, three months and one year postoperatively. As it is hypothesised that the anterior approach is superior to the posterolateral approach in terms of a faster recovery, mainly in the early recovery period (shorter hospital stay, faster return to normal ADL functioning), extra measurements of physical function, gait analysis and economic evaluation will take place two weeks postoperatively. The questionnaire will be sent to the patients a few days prior to the visit or – when patient do not have an email – will be filled in during the clinical outpatient visit. The filling in of the questionnaire will approximately take 30 to 45 min of patients’ time. A CONSORT flow chart is provided in Fig. 1. Demographic data, preoperative diagnosis, height, weight and Body Mass Index (BMI), ASA classification and the Kellgren and Lawrence (KL) score will be recorded preoperatively.

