The EuroQol questionnaire (EQ-5D) will also be administered. The health outcomes of the two approaches for THA will be assessed in terms of quality adjusted life years (QALYs). This reflects any differences in health-related quality of life based on the patients’ responses to the EQ-5D questionnaire preoperatively and at up to three points after hospital discharge (six weeks, three months and one year postoperatively). The EQ-5D is a generic questionnaire and consists of 5 questions regarding health-related quality of life [34]. The EQ-5D will also be used as a preference-based measure of health status for the cost-effectiveness analysis [35].

Next to the previous mentioned questionnaires the global rating of change will be assessed [36]. A global rating of change is a single item with which the overall (global) perceived improvement in physical functioning following THA can be assessed. This question is scored on a 7-point likert scale (1 = completely recovered; 2 = much improved; 3 = slightly improved; 4 = not changed; 5 = slightly deteriorated; 6 = much deteriorated; 7 = worse than ever), and asks for the change in physical functioning following THA.

The International Consultation of Incontinence Questionnaire-Short Form (ICIQ-SF) will be administered to evaluate whether THA has influence on urine incontinence [37]. The ICIQ-SF is a subjective questionnaire and is a recommended method to assess the grade of urine incontinence [38]. It consists of four questions on the frequency and volume of urine incontinence and its influence on daily life [37]. With the posterolateral approach the short external rotators of the hip are detached of the greater trochanter. Since the obturator internus muscle is connected to the pelvic floor musculature detachment of this muscle may have a negative effect to urine continence [39, 40], whereas with the anterior approach the pelvic floor remains undisturbed.

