### Statistical analysis

To analyse the data SPSS (Statistical Package for the Social Sciences, Chicago, Illinois) will be used. A *p*-value of < .05 will be considered to indicate statistical significance. Descriptive statistics (means and standard deviations) will be used to describe the subject characteristics and the results of the groups. The PASS score is determined by assessing the score on the HOOS of patients who are satisfied with their actual physical state and symptoms. PASS scores will be determined for the measurements made at six weeks, three months and one year postoperatively. The satisfaction question, which is asked on a four-response Likert scale, will be dichotomized into “satisfied” (i.e. the patients who are “very satisfied” or “somewhat satisfied”) and “unsatisfied” (i.e. the patients who are “somewhat dissatisfied” or “very dissatisfied”) [30, 32]. This dichotomized variable will then be used as anchor to calculate cut-off values on the HOOS to determine the PASS score. Next, a ROC analysis will be conducted, using the satisified/dissatisfied variable as anchor. As optimal cut-off value will be the one that maximizes the sum of sensitivity and specificity [30].

After that, all patients will be categorized as responders (i.e. a score on the HOOS beyond the PASS score) and non-responders. Chi-square tests will be used to determine potential differences in the proportion of responders between the study and control group at the above-stated time-points. Additionally, odds ratios with corresponding 95% confidence interval (CI) will be calculated. This ratio represents the odds of being a “responder” for the study group, compared to the control group. An odds ratio larger than 1 favours the study group and the point estimate of the odds ratio is considered to be statistically significant if the 95% CI does not include the value of 1.

Changes in physical activity, participation and gait function will be analyzed with Generalized Estimating Equations (GEE) analyses [51]. Analysis of Variance (ANOVA) will be used to assess differences in urine incontinence (ICIQ-SF), radiographic measurements, surgical time, blood loss and length of hospital stay between the study and control group. Differences in complication rates will be assessed by means of a Chi-square test.

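### The only schedule given for the WHODAS II Participation subscale omits a preoperative assessment, although the general schedule has one and the analysis is of changes in participation

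*Protocol article*

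**What the plan says.** The Participation section is the only place with a schedule specific to the WHODAS II subscale. It says that the subscale "will be assessed six weeks, three months and one year postoperatively". It adds that the subscale has ten items and describes the recall period: "The last 30 days are taken into consideration when answering the questions".

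Two general statements cover measurement as a whole. The Measurements section says: "Standard measurement will take place preoperatively, and six weeks, three months and one year postoperatively". The abstract, under Methods/design, says: "Measurements will take place preoperatively, two and six weeks, three months and one year postoperatively". Neither names WHODAS II, and neither excludes it. For the additional early visit, the Measurements section says that "extra measurements of physical function, gait analysis and economic evaluation will take place two weeks postoperatively"; participation is not in that list.

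The Statistical analysis section says: "Changes in physical activity, participation and gait function will be analyzed with Generalized Estimating Equations (GEE) analyses". It states neither the time from which change is counted nor any baseline covariate.

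**The concern.** An analysis of change needs a starting value. For participation, the instrument's own schedule begins six weeks after surgery, so on that text the natural starting value, the score before surgery, is not collected. The other two outcomes in the same GEE sentence, physical activity and gait function, have no visit list of their own and so fall under the general schedule with its preoperative visit. Participation is the only one of the three with a separate list, and that list starts after the operation.

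At stake is one secondary outcome. A centre working from the Participation section would leave the subscale out of the preoperative questionnaire, and a missed preoperative score cannot be recovered later. The analysis would then have no preoperative reference for change and no baseline to adjust for.

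**Working it through.** The article gives no figure on this point to reproduce, so the check compares the texts and then looks at what follows from them.

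**1. The schedules side by side**

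| Place in the protocol article | Preoperative | 2 weeks | 6 weeks, 3 months, 1 year |
|---|---|---|---|
| Abstract, Methods/design (general) | yes | yes | yes |
| Measurements (standard visits) | yes | no | yes |
| Measurements (extra visit: physical function, gait, economic evaluation) | – | yes | – |
| EQ-5D, in Physical functioning and health-related quality of life | yes | no | yes |
| WHODAS II, in Participation | not named | not named | yes |

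The EQ-5D and WHODAS II share the same three postoperative visits. For the EQ-5D the text names the starting point, "preoperatively and at up to three points after hospital discharge"; for WHODAS II it does not. The missing two-week visit agrees with the list of extra measurements, which suggests that the WHODAS II list was written for this instrument. The missing preoperative visit has no such counterpart elsewhere in the article.

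**2. Can six weeks serve as the reference?**

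Let d6 and d12 be the between-arm differences in participation at six weeks and at one year, with positive values favouring the anterior approach. The between-arm difference in change from six weeks to one year is d12 − d6. If the anterior approach helps early (d6 > 0) and the arms later converge (d12 = 0), this equals −d6, and an early benefit appears as a disadvantage of the same size. This pattern matters here because the Measurements section expects the advantage mainly in early recovery.

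Nor does the recall window reach back to the preoperative state. Six weeks is 42 days, and 42 − 30 = 12, so the six-week answers cover roughly days 12 to 42 after surgery.

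**3. What a baseline could add in precision**

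The documents give no correlation r between the preoperative and follow-up scores, so the values below are assumptions. For a single follow-up visit, relative to comparing follow-up scores alone:

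- Adjusting for baseline multiplies the variance of the between-arm difference by 1 − r². At r = 0.4 this is 1 − 0.16 = 0.84; at r = 0.6 it is 1 − 0.36 = 0.64.
- Analysing simple change scores multiplies it by 2(1 − r), assuming equal variances at both times. At r = 0.4 this is 1.2; at r = 0.6 it is 0.8.

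The gain therefore comes from using the score as a covariate. Subtracting it could lose precision when r is below 0.5. Neither factor carries over exactly to a GEE over three visits.

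**The case against.** The strongest reply is that the general schedule already supplies the baseline. The abstract and the Measurements section both place a measurement before surgery, and the three visits in the Participation section are exactly the standard postoperative ones. The list may only be saying when the subscale is repeated and that it is not part of the two-week visit. That reading is possible. A reader might infer that the trial has been designed without a preoperative participation score; the documents do not establish this, and the omission may be one of wording. What remains is that the general statements do not name the instrument while the specific one does, so a reader has reason to follow the specific one.

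It can also be said that the article elsewhere lists only postoperative times where a preoperative comparison is intended: PASS is determined after surgery and then compared with the preoperative state. This is a weak parallel, because PASS is by construction a state reached after treatment.

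A third reply is that change may mean the course from six weeks to one year, which the listed visits do support. This is correct as far as the wording goes, since no reference time is stated. It leaves the difficulty that six weeks lies after randomisation and surgery.

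Finally, the aim is to compare two approaches, and randomisation makes the comparison at each postoperative visit valid without a baseline. This stands in full. It is also true that the article plans no baseline adjustment for this outcome, so the variance factors describe an available gain and not a loss from anything planned.

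**Conclusion.** The point holds as an inconsistency between the Participation section on one side and the general schedule and the planned analysis of changes on the other. Taken literally, the Participation section leaves change from the preoperative state inestimable and provides no baseline score.

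Its reach is limited. It concerns one secondary outcome. The primary PASS analysis and the sample size of 260 are unaffected. A reader might infer that the participation comparison is biased, or that a stated share of the patients is in effect lost; neither follows. The randomised postoperative contrasts are sound, and the variance factors of 0.84 to 0.64 rest on an assumed correlation of 0.4 to 0.6 at a single follow-up.

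The conclusion assumes that no other trial document, and no entry in the flow chart (Fig. 1, not available for this check), places the subscale at the preoperative visit. If one does, only the wording of the article needs correcting.

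**What to change.** Amend the Participation section so that the subscale is listed in the preoperative questionnaire as well as at the three postoperative visits. In the Statistical analysis section, state that the preoperative score is the baseline in the GEE for participation, preferably as a covariate, and state the time from which any change is counted.

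For patients operated on without a preoperative score, describe the analysis as a comparison of postoperative levels and make no claim about change from before surgery.

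The cost is ten extra items, a few minutes per patient, on a questionnaire that the Measurements section puts at 30 to 45 minutes. No extra visit is needed. The amendment is worth making early, since it helps only patients who have not yet had surgery.

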#### Economic evaluation

An economic evaluation will be conducted to gain insight into cost-effectiveness of the anterior approach compared to the posterolateral approach for THA. After completion of the data collection, the health status, as determined by means of the EQ-5D, will be related to costs in additional economic analyses. These analyses will provide information on the probable cost-effectiveness of the anterior approach compared to the posterolateral approach for THA in the Dutch healthcare system.

The evaluation will be performed from a societal perspective; costs within and outside the healthcare sector will be included. Costs will be registered prospectively, i.e. within the framework of the current study, for all the included patients. A standardised questionnaire on medical costs after THA will be administered at two and six weeks, three months and one year postoperatively. The questionnaire is set up by the Medical Technology Assessment (MTA) and is used in the cost-effectiveness analyses. It contains 11 questions on indirect medical and non-medical issues regarding the THA outside of the hospital. Medical questions include hospital readmissions, visits to the hospital and/or other (paramedical) healthcare workers. Non-medical questions concern patients’ living and working situation.

The direct medical costs, such as the use of the operative theatre, hospital admission and additional interventions (e.g. blood transfusions) will be compared between the two approaches. Most salient cost advantages of the anterior approach are expected in the area of hospitalization costs. Of the various nonmedical costs, informal care costs are assumed to be substantial in the targeted population and will be registered in detail (e.g. visits to the general practitioner, physical therapy). In order to facilitate comparisons with other economic evaluations, unit prices (i.e. the price of one unit of each included cost type) are based on Dutch standard prices [49]. True costs of used resources will be estimated when standard prices are not available.

### Sample size calculation

Escobar et al. [30] showed that 70% of patients achieved an acceptable symptom state (PASS) at three months following THA, which means they have a positive PASS. The hypothesis is that the anterior approach results in a larger proportion of patients with a positive PASS at three months following THA. A difference of 20% in the proportion of patients with a positive PASS between the anterior approach and the posterolateral approach is considered clinically significant, as is described is described in the OMERACT-OARSI criteria [50]. Hence, based on the results of Escobar et al., a sample size of 60 patients in each study subgroup is needed to detect this difference of 20%, with a power of 80% and an alpha of 5%. Hence, each arm of the RCT needs to contain 120 patients. Based on previous experience, it is expected that approximately 10% will be lost in the follow-up. Hence, the total sample size will be set at 260 patients.

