It is expected that around 30% of the patients are ineligible or refuse to participate in the study. Hence, approximately an inclusion period of 24 months will be needed to include 260 patients.

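### A total of 260 does not leave 120 evaluable patients per arm after the plan's own 10% loss; the power cost is a point or less, and the 80% per stem subgroup also assumes an even stem split

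*Protocol article*

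**What the plan says.** The Sample size calculation section of the protocol article builds its total in steps.

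- The reference rate comes from a cited cohort that "showed that 70% of patients achieved an acceptable symptom state (PASS) at three months following THA".
- The effect to detect is "A difference of 20% in the proportion of patients with a positive PASS between the anterior approach and the posterolateral approach", with the anterior approach expected to do better.
- With 80% power and 5% alpha, this gives 60 patients in each study subgroup. There are two stem subgroups per approach, so "Hence, each arm of the RCT needs to contain 120 patients".
- For attrition, "it is expected that approximately 10% will be lost in the follow-up".
- The conclusion is "Hence, the total sample size will be set at 260 patients".

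The Study population and recruitment procedure section repeats the total: "an inclusion period of 24 months will be needed to include 260 patients". It describes one allocation set per stem type without giving the size of either. Stem type is decided by the surgeon's reading of bone stock and by age. The Statistical analysis section compares responders between study and control group with a chi-square test and describes no test by stem type.

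**The concern.** The section presents 260 as the result of allowing for about 10% loss on a requirement of 240. Neither usual way of making that allowance gives 260, and applying the stated loss to 260 leaves fewer patients than the section says are needed. Requirement, loss and total are all printed in one paragraph, and they disagree.

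There is a second, related point. The 80% belongs to 60 v 60 within one stem type, and doubling 60 to reach 120 per arm presumes two stem sets of equal size. Patient characteristics decide stem type, and the article states only an overall target.

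What is at stake is how the stated power is read. Someone who took 80% as the power within each stem subgroup would rely on a figure that needs both a loss of at most 7.7% and an even stem split.

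**Working it through.** **Inputs from the protocol article.** Reference proportion 70%; difference 20 percentage points in favour of the anterior approach, hence 90%; alpha 5%; power 80%; 60 per cell (approach by stem type); 120 per arm; loss about 10%; total 260. The sample size section does not say whether the test is one- or two-sided. I take it as two-sided, in line with the chi-square test and 95% confidence interval in the Statistical analysis section.

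**Step 1: reproduce the 60 per cell.**
- Unpooled variance: n = (1.960 + 0.842)² × (0.70×0.30 + 0.90×0.10) / 0.20² = 58.9, so 59.
- Pooled variance: n = [1.960 × √(2×0.80×0.20) + 0.842 × √(0.21 + 0.09)]² / 0.20² = 61.6, so 62.
- Arcsine formula: 59.01, so 60.

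The stated 60 is reproduced.

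**Step 2: the allowance for loss.**
- Requirement: 4 × 60 = 240.
- Dividing by the retained fraction: 240 / 0.90 = 266.7, so 267. Rounding up per cell, 60 / 0.90 = 66.7, so 67, and 4 × 67 = 268.
- Adding 10%: 240 × 1.10 = 264.
- What 260 leaves: 260 × 0.90 = 234, which is 117 per arm and 58.5 per cell.
- Loss that 260 can absorb: (260 − 240) / 260 = 7.7%.

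So 260 falls 7 short of 267 (8 short of 268), and 234 is 6 below the required 240.

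**Step 3: power per stem subgroup with equal stem sets.** The exact figures enumerate all outcomes of the uncorrected chi-square test at 70% v 90%.

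| Patients per approach in the subgroup | Exact chi-square | Unpooled formula | Pooled formula |
|---|---|---|---|
| 60 v 60 (as planned) | 80.2% | 80.7% | 78.9% |
| 59 v 59 | 80.5% | – | 78.2% |
| 58 v 59 | 79.5% | – | – |
| 58.5 (after 10% loss) | – | 79.8% | 77.9% |
| 58 v 58 | 79.7% | – | 77.5% |

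Within any one method, the shortfall costs a point or less: exact 80.2 − 79.5 = 0.7; unpooled 80.7 − 79.8 = 0.9; pooled 78.9 − 77.9 = 1.0. Exact power does not rise smoothly with n, which is why 59 v 59 lies slightly above 60 v 60.

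**Step 4: power of the overall comparison.** At 117 per arm, exact power is 97.7% and the pooled formula gives 97.3%.

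**Step 5: uneven stem sets (illustration only).** The article gives no expected stem mix, so the splits below are assumed. With 234 evaluable patients:
- 40:60: the smaller set has 234 × 0.40 / 2 = 46.8, about 47 per approach; exact power 70.5% (pooled 68.2%).
- 30:70: the smaller set has 234 × 0.30 / 2 = 35.1, about 35 per approach; exact power 56.5% (pooled 55.5%).

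**The case against.** **The loss figure is approximate.** The text says about 10% over a follow-up that runs to one year, whereas the sample size hypothesis concerns three months. Loss by then may be lower, and 260 is within 3% of 267. This is fair and is a reason to treat the point as minor. It does not make the step correct: no other loss figure is given, and both usual calculations exceed 260.

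**The 60 is not a tight minimum.** The unpooled formula asks for 59, and 59 v 59 has exact power of 80.5%. Expected cells of 58.5 are half a patient below that. This stands. A reader might infer that power drops to 78%, but that figure uses the pooled formula, which gives only 78.9% at 60, before any loss. About half of its distance from 80% is the choice of formula.

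**No described analysis is at risk.** The Statistical analysis section tests study against control group overall, and that test keeps about 97.7% power. A reader might infer that the trial is underpowered, or that a null result in the smaller stem set would mislead. The article supports neither: it describes no stem-specific test. What remains is that the sample size section attaches its 80% to the subgroup.

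**Sizes of the stem sets may be fixed elsewhere.** Lengths of allocation lists and caps per set are details that an article often leaves to the full protocol. This also stands. A reader might infer that the stem mix is left uncontrolled, but the article does not show that; it only does not show an even split to be secured. The 71% and 56% illustrate this dependence and do not predict the mix.

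**Conclusion.** The step from 240 with about 10% loss to 260 is wrong on the section's own inputs: 260 leaves 234 and covers 7.7% loss, while 10% needs 267 or 268. The consequence is small. With equal stem sets, power per subgroup after 10% loss is about 79.5-80%, just under the stated 80%, and the planned overall comparison is unaffected.

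The 80% per subgroup is also conditional on roughly equal stem sets, and the article does not state that condition.

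These results assume 70% v 90%, a two-sided 5% test, 1:1 allocation and a loss of exactly 10% spread evenly over the cells. Severity is minor. Confidence is high for the arithmetic and lower for the stem split, because the expected mix is unknown.

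**What to change.** Reword the end of the Sample size calculation section and keep 260:

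- State that 260 allows for a loss of 7.7%, and that at 10% loss with equal stem sets it gives just under 80% power in each stem subgroup.
- State that the 80% per subgroup is conditional on an even split between cemented and uncemented stems.
- State that the planned overall comparison of the two approaches has about 97% power at 117 per arm.

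The alternative is to keep the 10% allowance and raise the total to 267, or 268 for four equal cells, at the cost of 7 or 8 more patients. The gain of a point or less in subgroup power does not call for that. The first option costs wording only and needs no extra patients.
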